#### Study variables

In this study, the designed interventions will be considered as an independent variable, while awareness, attitude and practice of fathers about participation in perinatal care will be considered as dependent variables.

#### Data collection

The tools used in the quantitative phase of this research are researcher-made questionnaires. The first part consists of demographic and reproductive characteristics; while the second part of the questionnaire is to assess the awareness, attitude and practice of fathers which will be completed before the intervention and 3 months after the intervention. The knowledge and attitude questionnaires will be completed by fathers and father’s practice questionnaire will be completed by their wives. The awareness questionnaire consists of 28 questions, which have three options: “correct”, “false” and “not sure.” The attitude questionnaire, which consists of 23 questions, is based on the Likert scale of 5 options with the answer “I totally agree”, “agree”, “do not comment”, “disagree”, and “completely disagree”. The practice questionnaire has 23 questions, based on the Likert scale, with the options “Never”, “rarely”, “sometimes”, “most often” and “always”.

#### The implementation method

The researcher will implement the proposed intervention after obtaining a permit from the Ethics Committee of Tabriz University of Medical Sciences and performing the necessary coordination with the designated centers’ officials. At first, through prenatal care records, the list of pregnant women with a gestational age of 20 to 22 weeks will be extracted and through phone, they will be invited together with their husband to participate in the research. After reaching the sample, knowledge and attitude of fathers in the intervention and control groups will be measured by questionnaires before intervention and their practice about participation in prenatal care will be measured by using questionnaire completed by their wives. After the implementation of the intervention program, the questionnaires will be completed again in the intervention and control groups.

#### Data analysis

The collected data will be analyzed using descriptive statistical methods (mean, standard deviation, minimum and maximum) and inferential statistics (One way analysis of variance, paired t-test, Chi-square, Fisher’s exact test, and Mann-Whitney) and by using SPSS 23 software.

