### Phase III: Quantitative study

#### Type and direction of the quantitative study

The quantitative phase of the research will be implemented as a three-group semi-experimental study.

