#### Sample size

The sample size calculation is based on the results of previous studies, based on knowledge, attitude and practice variables using G-power software. The maximum sample size based on the practice variable and considering the data [power 95%, two sided α = 0.05, sd_2_ = 6.34, m_2_ = 88.81, sd_1_ = 14.69, m_1_ = 76.18] will be calculated with 22 people in each group, and due to probability of 10% loss, total sample size will be considered as 24. The final sample size will be determined based on the pilot study.

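### The named between-group tests do not fit the plan's own figures: equal-variance ANOVA despite planning SDs of 14.69 and 6.34, and a two-sample rank test for three arms

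*Protocol article*

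**What the plan says.** The Phase III study "will be implemented as a three-group semi-experimental study", and the Sampling method section specifies two intervention groups and one control.

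The Sample size section takes its inputs from earlier work ("The sample size calculation is based on the results of previous studies"). For the practice score it uses "sd_2_ = 6.34, m_2_ = 88.81, sd_1_ = 14.69, m_1_ = 76.18" with "power 95%, two sided α = 0.05". The result "will be calculated with 22 people in each group", raised to 24 for 10% loss. The final size is left to a pilot study. The section does not say which SD belongs to the control condition and gives no SD for a third arm.

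The Data analysis section is one sentence. The inferential methods are one-way ANOVA, the paired t-test, chi-square, Fisher's exact test "and Mann-Whitney) and by using SPSS 23 software". It does not tie tests to outcomes. It names no unequal-variance version of ANOVA, no three-group rank test and no pairwise procedure.

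**The concern.** Two of the named methods sit badly with the rest of the protocol.

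- **ANOVA.** One-way ANOVA estimates a single error variance across all arms. The sponsor's own planning figures say that the arms may differ more than fivefold in variance. A pooled error term is then too small for comparisons involving mostly wide arms and too large for comparisons among narrow ones.
- **Rank test.** The outcomes are sums of Likert or three-option items, so a rank analysis may well be wanted. The only rank test named for comparing groups cannot give an overall comparison of three arms. Three unadjusted pairwise tests at 5% would have a familywise error of about 1 - 0.95^3 = 14% if treated as independent.

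At stake is whether the overall p-value and the pairwise intervals for awareness, attitude and practice mean what they claim.

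**Working it through.** **Inputs from the Sample size section:** "sd_1_ = 14.69, m_1_ = 76.18"; "sd_2_ = 6.34, m_2_ = 88.81"; n = 22 per group; two-sided alpha 0.05; power 95%. I read the 24 after loss as a per-group figure.

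**Step 1: reproduce the stated sample size.**
- Difference = 88.81 - 76.18 = 12.63.
- Root-mean-square SD = sqrt((14.69^2 + 6.34^2)/2) = sqrt((215.80 + 40.20)/2) = 11.31.
- Standardised difference = 12.63/11.31 = 1.116.
- Noncentral-t power is 0.942 at 21 per group and 0.951 at 22.

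The stated 22 is therefore reproduced using both SDs, so unequal spread is part of the sponsor's own planning.

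**Step 2: variance ratio.** (14.69/6.34)^2 = 5.37.

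**Step 3: pooled against actual standard error, 22 per arm.** The third SD is not given. I assume that it equals one of the two stated values and run both cases.

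*Case A, one wide arm and two narrow (14.69, 6.34, 6.34).*
- Error mean square = (215.80 + 40.20 + 40.20)/3 = 98.7. Pooled SE = sqrt(2 x 98.7/22) = 3.00.
- Wide against narrow: actual SE = sqrt(256.0/22) = 3.41, ratio 0.88.
- Narrow against narrow: actual SE = sqrt(80.4/22) = 1.91, ratio 1.57.

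*Case B, two wide arms and one narrow (6.34, 14.69, 14.69).*
- Error mean square = (40.20 + 215.80 + 215.80)/3 = 157.3. Pooled SE = sqrt(2 x 157.3/22) = 3.78.
- Wide against narrow: actual SE = 3.41, ratio 1.11.
- Wide against wide: actual SE = sqrt(431.6/22) = 4.43, ratio 0.85.

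**Step 4: type I error by simulation** (100,000 null trials per case, normal data, 22 per arm, nominal 5%; 20,000 trials for Mann-Whitney).

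| Test | Case A | Case B |
|---|---|---|
| Ordinary F, overall | 6.6% | 5.5% |
| Welch ANOVA, overall | 4.9% | 5.0% |
| Pooled pairwise, unadjusted: wide v narrow | 8.8% | 3.1% |
| Pooled pairwise, unadjusted: like v like | 0.3% | 9.3% |
| Tukey per pair: wide v narrow | 4.2% | 1.0% |
| Tukey per pair: like v like | 0.05% | 4.5% |
| Tukey, familywise | 6.3% | 5.5% |
| Separate two-group t-tests | 4.9 to 5.4% | 4.9 to 5.2% |
| Mann-Whitney, pairwise | 4.9 to 6.3% | 4.9 to 6.2% |

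With truly equal variances Tukey runs at about 1.9% per pair, so it keeps the same imbalance at a lower level. At 24 per arm the picture is unchanged (ordinary F 6.3% and 5.7%).

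**Step 5: does the sample size survive?** The Welch two-sample test has about 28.6 degrees of freedom and noncentrality 12.63/3.41 = 3.70. Power is 0.947 at 22 per group and 0.963 at 24.

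**The case against.** The strongest reply is that the Data analysis section only lists test families. Post hoc procedures and assumption checks are commonly left to an analysis plan, which is not at hand, and SPSS offers Welch and Games-Howell. This stands as far as the pairwise figures go: they apply only if the pooled error term is used, and separate two-group tests hold close to 5%. It does not remove the mismatch in what is named, which is an equal-variance ANOVA set against unequal planning SDs, and a two-sample rank test for three arms.

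A second reply is that the harm is small in ordinary practice. The overall F is off by 0.5 to 1.6 percentage points, and Tukey limits familywise error to about 6%. That is correct. What remains is the uneven split of error between pairs.

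A reader might infer four stronger conclusions that the documents do not support:

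- *That pairwise intervals will be wrong.* No pooled pairwise procedure is specified.
- *That programme-versus-control intervals in particular are too narrow.* Neither SD is labelled as the control's and the third is absent. If both programme arms had the large SD, that comparison would be too strict and programme-versus-programme too liberal.
- *That the comparison of the two programmes loses about half its power.* This needs an assumed difference between programmes, such as 5.5 points. The documents give none, and the Phase III objective states no such hypothesis.
- *That Mann-Whitney contributes to the standard-error problem.* It uses no pooled SE, and pairwise use is legitimate. Its shortcoming is only that it gives no overall three-group test.

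**Conclusion.** The point holds in a conditional form. One-way ANOVA is a poor match for the plan's own SDs, and Mann-Whitney cannot serve as the overall rank test for three arms. With 22 per arm the overall F test runs at about 5.5 to 6.6%. If the pooled error term is carried into pairwise comparisons, some intervals are 12 to 15% too narrow and others 11 to 57% too wide, with unadjusted type I error of about 9% and about 0.3 to 3% respectively.

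These sizes assume normal scores, equal arms, and a third SD equal to one of the two stated. The SDs are provisional values from earlier studies, and the pilot may change them. The change is worth making because it is cheap, but it does not overturn the design.

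**What to change.** Replace one-way ANOVA with Welch's ANOVA followed by Games-Howell pairwise comparisons. Alternatively, use a linear model adjusted for the baseline score with HC3 standard errors, since the questionnaires are already completed before the intervention. Name Kruskal-Wallis as the three-group rank test, with Dunn or Mann-Whitney tests only as multiplicity-adjusted follow-up.

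The cost is one or two sentences. Welch, Games-Howell and Kruskal-Wallis are available in SPSS. Welch's ANOVA also held its level when the simulated variances were equal (4.9%). The planned 22 per group remains adequate for a single Welch comparison. Adjusting for three pairs costs some power whichever error term is used: at level 0.05/3 the pooled two-group calculation gives 88% at 22 per group and 91% at 24.

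The change leaves one problem untouched. Each arm comes from one clinic, so any clinic effect remains mixed with the arm effect, and better standard errors cannot separate them.

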#### Integration of the qualitative and quantitative data

The results of the qualitative and quantitative phases of the study will be integrated and finally, a program for father’s participation in perinatal care will be provided.

## Discussion

Considering that fathers’ participation in perinatal care is an important key factor in the improvement of mother’s and infant’s health, therefore, the need for fundamental interventions in this field is essential. In this mixed methods study, sequential exploratory approach will be used for providing an interventional program sensitive to the culture and conditions of the Iranian society for men’s participation in perinatal care. Sequential exploratory approach is a known method for researching, especially when little information is available about the study subject. It is an appropriate method for achieving participants’ experiences. When one method is not sufficient for revealing the study subject, it is better to use a combination of two methods [18]. Using a mixed methods study will help the researcher gain a more comprehensive understanding of the phenomenon and relate its different aspects with each other [19, 20]. Since the present research question has a new multidimensional nature and the researcher is not able to predict the factors that will affect the subject, therefore, it seems that the use of a mixed methods study and the application of both the qualitative and quantitative methods will be an appropriate way to reach the goals of the study. Men’s participation in all of the stages of the mother’s and infant’s life has significant effects on their physical and psychological health; and international conducted studies have mentioned the great potential of fathers for participation during pregnancy, delivery and postpartum periods on decreasing mothers’ mortality and morbidity rates [21]. According to the report of the World Health Organization, 99% of these deaths could be prevented [22] and also, addressing the obstacles for using perinatal care and providing a supportive environment in the society and the family for women’s access to these care have been mentioned as the main strategies for decreasing mothers’ mortality rate [23]. Therefore, it seems that the results of the present study will help policymakers, managers of health deputies, healthcare providers and families especially husbands to perform their essential roles in improving fathers’ participation in perinatal care by using the presented interventional program, and consequently have a positive effect on mothers’ and infants’ health and decrease their rate of mortality and morbidity.

## Abbreviations

AIDS: Acquired Immune Deficiency Syndrome
ICPD: International Conference on Population and Development
MDGs: Millennium Development Goals
STD: Sexually Transmitted Diseases
